**n = 36.3058**

delta = 1

sd = 1.5

sig.level = 0.05

power = 0.8

alternative = two.sided

NOTE: n is number in *each* group

Patients who are with drawn are not replaced.

Differences in PWV will be statistically examined using paired t tests.

The secondary effect parameters will also be examined using this statistic method. For the groups as a whole two sample t test will be applied. If data do not fit the normal distribution they will be transformed.

1. ***Quality control***

Normal procedures for quality control will be followed, see ICH GCP Guidelines. Data will be monitored by The GCP unit at Copenhagen University Hospital, Bispebjerg Hospital, [name], [name], [name]. As informed consent is given, a permission from the participant for the Danish Medicines Agency and the GCP unit to have access to the patient’s hospital medical files will be sought. A copy of the text is available (in Danish).

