### 3.2 Design

The study is a prospective, randomized, controlled, parallel group, phase IV study.

| Week number | -4 | 1 | 2 | 4 | 8 | 12 | 16 | 20 | 24 |
| --- | --- | --- | --- | --- | --- | --- | --- | --- | --- |
| Visit number |  | 1a/1b | 2 | 3 | 4 | 5a/5b | 6 | 7 | 8a/8b |

A BP target of 120-130/80-90 is set and investigators will strive to keep this constant in patients throughout their enrolled period. Therefore a run-in period of 4 weeks has been planned. All patients are to continue on their normal medication including blockers of RAS, which most of these patients receive before enrolment. If anti-hypertensive treatment needs to be intensified, this is done by adding beta blocker, calcium antagonist or methyldopa. If BP is lower than target pressure medication will be withdrawn, primarily via reduction in calcium antagonism or beta blockade, while RAS-blockade in the initial form is aimed to be kept as it was.

If study participants fail to tolerate the full dose of eplerenone 50 mg once daily, dose will be reduced to 25 mg once daily. In case of the patients receiving potassium supplements at time of enrolment these will be withdrawn before start of intervention.

Participants are randomized after the run-in period and are given consecutive numbers of identification.

The study plan is identical for the two groups.

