### 3.3 Endpoints

Primary endpoint is the difference in PWV measured by the tonometer (Millar, Houston, Texas, USA) and using the SphygmoCor® hard- and software.

Secondary endpoints are pulse wave morphology, evaluated by the AIx, BP, subendocardial viability ration (SEVR), heart rate, time to reflection (TR), ejection duration (ED), pulse pressure (PP), kidney function (estimated glomerular filtration rate (eGFR)), p-creatinine, AASI and albuminuria.

P-potassium and p-creatinine are used for safety monitoring.

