AMBPs are automatically measured blood pressures during ordinary daily activities for a time period of approximately 24 hours. AMBP has been found reproducible in population studies (25-30), hypertensive populations (46) and diabetics (47). The reproducibility of AASI has been proven less reliable in an essentially hypertensive population (48) . The brachial BP is measured in the office using the ABPM equipment on the non-dominant arm. After manual measurements the apparatus will automatically measure the BP every 15 minutes in daytime, which is defined from 7 am until 11 pm. Hereafter the measurements will be performed every 30 minutes from 11 pm till 7 am (49). All patients receive a diary in which they are to make notes of physical activity, meals and rest as well as bedtime and rising time in the morning. For calculation of AASI a minimum of 21 readings of BP is required. These must be spread out over the whole period with at least 7 successful readings during night time. AASI is calculated in the following manner: (1-(the slope of diastolic BP/slope of systolic BP)). It follows that the stiffer the arterial tree, the more the regression line will go towards 0 and AASI thus towards 1. Previous studies have provided references for AASI in the background population. AASI for normotensive individuals is 0.57. In younger individuals AASI is 0.53 increasing to 0.72 in the elderly (30).

*Intervention – study medication*

The study medication is eplerenone, a selective aldosterone receptor antagonist. It is an approved drug, which in this study will be used on a non-appraised indication. The Summaries of Product Characteristics (SPC) in Danish will be used as reference document for evaluation of possible side effects and will be accessible at the site of investigation when the study is initiated.

Initial recommended dose is 25 mg once daily. The dose will be increased to 50 mg eplerenone in once daily dosing after 1 week. In this study eplerenone will be added to the study participants’ usual medication. The manufacturing company Pfizer Aps has been informed of the study.

*Control*

The control group will continue their usual medical therapy.

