## Statistics

Power calculations have been made based on a minimal clinically relevant difference on the primary end point PWV of 1 m/s. It has been shown that an increase of PWV of this size increases mortality by 39%(19).

From our own data we have a standard deviation of 1.5 on PWV. At a level of significance of 0.05 and power 0.8 a calculation of number of participants for each group should reach 37. We plan to include 40 patients in each group.

Two-sample t test power calculation

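### The protocol names a paired, within-patient t test for PWV and gives the randomised between-arm comparison no stated deciding role

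*Protocol*

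**What the plan says.** Protocol section 3.2 describes two concurrent randomised groups: "The study is a prospective, randomized, controlled, parallel group, phase IV study". Section 3.4 defines the comparator: "The control group will continue their usual medical therapy".

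Section 3.3 introduces the main outcome with "Primary endpoint is the difference in PWV measured by the tonometer". It does not say whether the difference is between arms or between visits.

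The Statistics section sizes the trial under the line "Two-sample t test power calculation". It uses a "minimal clinically relevant difference on the primary end point PWV of 1 m/s", a standard deviation of 1.5, two-sided significance level 0.05 and power 0.8. The result is n = 36.3058 in each group, given as 37, with 40 planned.

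Three consecutive sentences in the same section then give the analysis:

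- For the primary endpoint: "Differences in PWV will be statistically examined using paired t tests".
- For the rest: "The secondary effect parameters will also be examined using this statistic method".
- Then: "For the groups as a whole two sample t test will be applied".

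No sentence in the protocol says which of these tests answers the primary question.

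**The concern.** The only test tied by name to PWV is one that cannot use the control group. A paired t test needs two measurements on the same person, and eplerenone and control patients are different people. Applied to PWV it tests change from one visit to another within an arm. The secondary parameters inherit the same method.

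The sentence that could restore the randomised comparison names no endpoint and does not say that its result decides anything. An analyst following the text literally could report a significant fall in the eplerenone arm as the main result, or report a fall that is significant in one arm and not in the other. Neither is a test of eplerenone against control. Both can arise when the two arms change by the same amount.

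A common change is conceivable here. Section 3.2 provides for antihypertensive treatment to be adjusted in all patients, and the Background lists blood pressure among the independent influences on PWV. At stake is the trial's single primary conclusion. In addition, the stated 80% power was calculated for a different test from the one named for PWV.

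**Working it through.** **Step 1. Reproduce the plan's figure.** Inputs from the Statistics section: difference 1 m/s, SD 1.5, two-sided 0.05, power 0.8. The normal approximation gives n = 2 × (1.5/1)² × (1.960 + 0.842)² = 4.5 × 7.85 = 35.3, rounded up to 36. The noncentral t calculation gives 36.306 per group, which agrees with the stated 36.3058 and rounds up to 37. Power is 0.81 at 37 per group and 0.84 at the planned 40. The figure is right for a two-sample test.

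**Step 2. Does it fit the test named for PWV?** If 1.5 were the SD of within-patient differences, a paired test would need 19.67, so 20 patients in all. The 37 per group therefore belongs to the between-arm comparison, not to the paired test.

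**Step 3. What the paired test does when the drug has no effect.** Let both arms change by the same amount d. The SD of change is 1.5 × √(2(1 − ρ)), where ρ is the correlation between baseline and follow-up PWV. The noncentrality of the eplerenone-arm paired test at n = 40 is d × √40 / SD of change. The protocol gives neither d nor ρ, so both are assumptions. For d = 0.3 m/s:

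- ρ = 0.5: SD of change 1.50; noncentrality 0.3 × 6.325 / 1.50 = 1.26
- ρ = 0.7: SD of change 1.162; noncentrality 1.63
- ρ = 0.8: SD of change 0.949; noncentrality 2.00

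The table gives rejection probabilities with no drug effect and 40 per arm, from 20,000 simulated trials per row. Direct calculation of the paired column agrees to within 0.5 of a percentage point.

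| Common fall (m/s) | ρ | Paired test significant on eplerenone | Significant on eplerenone, not on control | Two-sample test on change |
|---|---|---|---|---|
| 0.3 | 0.5 | 24% | 18% | 5% |
| 0.3 | 0.7 | 36% | 23% | 5% |
| 0.3 | 0.8 | 50% | 25% | 5% |
| 0.5 | 0.5 | 54% | 25% | 5% |
| 0.5 | 0.7 | 76% | 19% | 5% |
| 0.5 | 0.8 | 90% | 9% | 5% |

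With no common change (d = 0) the paired test rejects in 5% of trials, and the discordant pattern occurs in 0.05 × 0.95 = 4.75%. The inflation comes entirely from the assumed common change.

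**Step 4. Does the sample size survive the correction?** A two-sample test on change from baseline, with 40 per arm and a true difference of 1 m/s, has power 0.84, 0.97 and 0.996 for ρ = 0.5, 0.7 and 0.8. Below ρ = 0.5 the SD of change exceeds 1.5, and a change score would have less power than planned. Analysis of covariance (ANCOVA) on baseline avoids this. Its residual SD is 1.5 × √(1 − ρ²), which is 1.30, 1.07 and 0.90 for the same three values and never exceeds 1.5.

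**The case against.** The strongest reply is that the section, read as a whole, describes a familiar scheme: paired tests within arms and a two-sample test between them. The third sentence plans a two-sample test, and the power calculation applies one to PWV with n per group. A reader might infer from the first sentence alone that the randomised comparison has been dropped or demoted. The documents do not support that, because a between-group test is planned and no test of either kind is called primary. They leave the randomised comparison without a stated role; they do not exclude it.

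A reader might also infer that the plan exceeds the 5% error rate as it stands. That is not supported either. The excess needs a change common to both arms, and section 3.2 aims to hold blood pressure steady and includes a four-week run-in, both of which should limit such drift. It also needs someone to claim efficacy from one arm's result, which the protocol nowhere says will happen.

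Finally, the choice of visit and the adjustment for baseline are often left to a statistical analysis plan, which is not at hand, so their absence is not counted here.

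These replies limit the claim but do not remove it. The protocol is not silent on the test for PWV. It names one that does not fit a parallel-group design, and the sentence that could repair this does not mention PWV. A later analysis plan would inherit the conflict.

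**Conclusion.** The point holds as a misfit between the named test and the design. Paired t tests are the only method tied to PWV and the secondary parameters, while the design and the sample size both call for a comparison of randomised arms. As worded, the plan allows efficacy to be judged from within-arm change, which ignores the control group and to which the stated power does not apply.

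The size is conditional. With no drug effect and an assumed common fall of 0.3 m/s, a claim based on the eplerenone arm alone would be wrong in about 24% to 50% of trials for assumed correlations of 0.5 to 0.8, against about 5% for the between-arm test. With no common change there is no inflation. The sample size calculation is correct for the between-arm test and is not at fault.

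This should be corrected before analysis because it governs the only primary conclusion.

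**What to change.** Replace the analysis sentences in the Statistics section with wording such as:

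> The primary analysis is the between-arm comparison (eplerenone versus control, as randomised) of PWV at week 24, using change from baseline or, preferably, ANCOVA adjusted for baseline PWV, with two-sided alpha 0.05. Secondary endpoints are also compared between arms. Within-arm paired changes are descriptive only.

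ANCOVA is preferred because its precision does not depend on the correlation reaching 0.5. PWV is already scheduled at baseline and at week 24, so the change needs no new measurements or patients and no new sample size. The cost is a rewording of a few sentences.

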### 3.13 Practical performance of study

Patients who fulfil the inclusion criteria and who are interested in participating in the study are informed about the study. The written information is handed out and will be thoroughly explained. A form of written informed consent is to be signed by the patient and the informant/investigator. If consent is given, dates for the study days will be given.

Demographic data will be registered.

Randomization: When inclusion criteria are met including the performance of a screening for PW measurements and the run-in period has been completed, patients are randomized to the active treatment arm with eplerenone or the control arm for 24 weeks.

Planning:

A deviation of ± 1 week from the initially planned date for visits is permitted. Collection of 24 hour urine is allowed for at time deviation of ± 3 days with respect to blood sampling. Participants’ visits are planned to be identical in both groups.

Visits are planned as shown below:

| ***Visit number*** | ***Time with reference to inclusion for the individual patient*** | ***Purpose of visit*** | ***Estimated time used for the visit*** |
| --- | --- | --- | --- |
|  | Screening | signing of written informed consent, PW measurement test, ECG, blood sampling, demographic data noted | 1-1½ hours |
| 1a | Week 1 | randomization, PW measurement, AMBP, blood sampling, 24 h urine, study medication handed out | 1 hour |
| 1b | Week 1 | return of AMBP device | 10 minutes |
| 2 | Week 2 | blood sampling, BP, increase in study medication | 30 minutes |
| 3 | Week 4 | blood sampling, BP, study medication handed out | 30 minutes |
| 4 | Week 8 | blood sampling, BP, study medication handed out | 30 minutes |
| 5a | Week 12 | PW measurement, AMBP, blood sampling, 24 h urine, study medication handed out | 1 hour |
| 5b | Week 12 | return of AMBP device | 10 minutes |
| 6 | Week 16 | blood sampling, BP, study medication handed out | 30 minutes |
| 7 | Week 20 | blood sampling, BP, study medication handed out | 30 minutes |
| 8a | Week 24 | PW measurement, AMBP, blood sampling, 24 h urine, study medication and packages returned | 1-1½ hours |
| 8b | Week 24 | return of AMBP device | 10 minutes |

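### The named t tests use one pair or one summary value per patient, although PWV is collected at baseline, week 12 and week 24 and no primary visit is named

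*Protocol*

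**What the plan says.** Section 3.3 defines the endpoint without a visit: "Primary endpoint is the difference in PWV measured by the tonometer". Statistics names paired t tests for differences in PWV. It then adds "The secondary effect parameters will also be examined using this statistic method" and "For the groups as a whole two sample t test will be applied". The last sentence is best read as the between-arm comparison, since the sample size is computed for a two-sample t test.

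The schedule is richer than these tests. In section 3.13 the week-12 visit consists of "PW measurement, AMBP, blood sampling, 24 h urine, study medication handed out", and pulse-wave measurement, ambulatory blood pressure and 24-hour urine are done at visits 1a, 5a and 8a (weeks 1, 12 and 24). Section 3.11 lists creatinine and eGFR, both secondary endpoints, at screening and at visits 1a, 2, 3, 4, 5a, 6, 7 and 8a.

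On losses, Statistics says "Patients who are with drawn are not replaced". Section 3.9 returns withdrawn patients to routine clinic care and describes no further study visits for them.

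**The concern.** A paired t test takes two values per patient and a two-sample t test takes one. Neither uses baseline, week 12 and week 24 jointly. If the week-24 value is missing and nothing is imputed, the week-12 value does not inform the week-24 comparison.

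This matters most when losses differ between arms. Several withdrawal grounds in section 3.9 correspond to effects that the Protocol itself expects from the drug: hyperkalaemia, a creatinine rise and unacceptable side effects. Ethical considerations lists hyperkalaemia and reduced kidney function among the drug's common side effects, and Adverse events and side effects says that unacceptable side effects lead to withdrawal. Controls only continue usual therapy. A comparison of completers could therefore set a selected eplerenone group against a nearly complete control group.

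The unnamed primary visit adds a second problem: the same t test could be run on week 12 or on week 24.

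**Working it through.** **Inputs from the Protocol (Statistics, 3.11, 3.13).** A "minimal clinically relevant difference on the primary end point PWV of 1 m/s"; "From our own data we have a standard deviation of 1.5 on PWV"; "At a level of significance of 0.05 and power 0.8"; two-sided; 40 planned per group. There are three PWV values per patient, and nine creatinine/eGFR values, of which seven follow visit 1a.

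**Inputs the Protocol does not give (assumed).** Correlation between visits, dropout rate per arm, and how dropout relates to PWV.

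**Step 1: the plan's own figure.** Two-sample power uses a noncentral t with noncentrality δ/(SD·√(2/n)) and 2n−2 degrees of freedom. With δ = 1, SD = 1.5, two-sided 0.05 and power 0.80, n = 36.3058 per group, exactly as stated. The sample size is not in question.

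**Step 2: room for losses.** 40 − 37 = 3 per group, or 3/40 = 7.5%.

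| Analysed per group | Power |
|---|---|
| 40 | 83.8% |
| 37 | 80.8% |
| 36 | 79.7% |
| 32 | 74.7% |
| 28 | 68.8% |

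This holds if 1.5 is the SD of the quantity compared. If it is the SD of a single reading and change is tested, the SD is 1.5·√(2(1−r)): 1.342 at r = 0.6 and 0.949 at r = 0.8. Power at r = 0.6 is then 83.5% even with 32 per group. Bias is therefore the larger issue, not power.

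**Step 3: bias under assumed unequal, outcome-dependent loss.** Simulated trials (3,000 per setting) used 40 per arm, SD 1.5, equal correlation r between visits, and true effects of −0.5 at week 12 and −1.0 at week 24. Loss occurs after week 12 and is likelier when PWV has changed unfavourably by week 12.

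| r | Loss, control / eplerenone | Completers' change difference (SE) | Estimate using week 12 |
|---|---|---|---|
| 0.6 | 5% / 20% | −1.075 (0.320) | −0.990 |
| 0.6 | 5% / 30% | −1.136 (0.344) | −0.996 |
| 0.8 | 5% / 20% | −1.058 (0.230) | −0.998 |
| 0.8 | 5% / 30% | −1.097 (0.239) | −1.000 |

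The completers' estimate overstates the effect by 0.06-0.14 m/s, which is about 0.058/0.230 = 25% to 0.097/0.239 = 41% of one standard error in the r = 0.8 rows, and similar at r = 0.6.

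**Step 4: check by hand, and why other assumptions give more.** The bias is approximately b × SD(week-12 change) × d. Here b is the slope of the week-24 change on the week-12 change, and d is the between-arm difference in completers' mean standardised week-12 change. Under equal correlation b = 0.5. The 30% rows give d = 0.136/(0.5 × 1.342) = 0.20 and d = 0.097/(0.5 × 0.949) = 0.20, which agree, as they should under one dropout model. In general b = (r₁₂,₂₄ − 2r₀ + 1)/(2(1 − r₀)), where r₀ is the correlation with baseline. With r₀ = 0.6 and r₁₂,₂₄ = 0.7, b = 0.5/0.8 = 0.625; with 0.7 and 0.85, b = 0.45/0.6 = 0.75. A tighter link between the two later visits therefore enlarges the bias. Simulations in that range, with 5% control and 19-29% eplerenone loss, give 0.13-0.21 m/s. Adjusting completers for baseline alone leaves 0.10-0.17 m/s. Including week 12 brings it to about zero.

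**Step 5: random loss.** There is no bias. Week 12 lowers the SE by about 3% or less: at 20% loss per arm and r = 0.6 it goes from 0.340 to 0.333, or 2.1%. Baseline adjustment helps more: the SE ratio to a change score is √((1+r)/2), which is 0.894 at r = 0.6 and 0.949 at r = 0.8, a gain of 11% and 5%.

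**Step 6: size of the model.** An unstructured covariance needs 2×3/2 = 3 parameters for weeks 12 and 24, but 7×8/2 = 28 for seven creatinine visits in at most 80 patients.

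**The case against.** A reader might infer that the Protocol drops every patient without week 24 and discards the week-12 data. It says neither. It names no visit and no missing-data rule. A t test is compatible with a week-12 analysis, with tests at both visits, or with an imputed or carried-forward value. A missing-data rule may properly stand in a statistical analysis plan that is not shown. This objection stands, so the point is confined to the tests that the Protocol does name.

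A two-sample t test is a valid randomised comparison and matches the sample size calculation. That also stands: this is a better method, not the correction of an invalid one.

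The bias rests on an assumed dropout model. No withdrawal criterion refers to PWV, so neither the size nor the sign is fixed by the documents. If patients with larger falls in PWV left instead, the bias would run the other way. The creatinine criterion applies at the first control visit, which the schedule suggests is week 2. Patients lost then have no PWV after baseline, and no model recovers it.

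A reader might also infer that most creatinine values are wasted and that the screening value should be a second covariate. With equal correlation of 0.8 this would cut residual variance from 1 − r² = 0.360 to 1 − 2r²/(1+r) = 0.289. The documents do not support relying on that. The many visits are there for safety, and screening precedes a run-in in which antihypertensive treatment may change (section 3.2), so equal correlation is doubtful.

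What survives is that the Protocol commits to t tests. Testing week 12 separately would not correct a week-24 comparison.

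**Conclusion.** The point holds as a worthwhile, inexpensive improvement. The stated tests do not use the three-visit design jointly, and the primary visit is open. Unequal withdrawal is plausible on the Protocol's own account of the drug's side effects.

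The possible bias is roughly 0.06-0.2 m/s on a 1 m/s effect. It rests on assumed drug-arm loss of about 20-30% that depends on the week-12 change, about 5% control loss, and correlations of 0.6-0.85. It is zero if loss is random, and the precision gained from week 12 is then small. The documents do not show that such bias will occur, and the stated sample size is correct on its own inputs.

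**What to change.** In Statistics, name week 24 as the primary visit. Replace the t tests for PWV, AASI, ambulatory blood pressure and albuminuria by a mixed model for repeated measures over weeks 12 and 24, with arm, visit, arm-by-visit and the baseline value. Report the week-24 between-arm difference with a 95% confidence interval.

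For creatinine and eGFR, use the same type of model over the on-treatment visits with the visit 1a value as baseline, and state in advance a simpler covariance structure in case the unstructured one does not converge.

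Add a sensitivity analysis for withdrawals. The model assumes data missing at random and recovers no PWV for patients who leave before week 12.

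The cost is one paragraph of text and some extra programming. No visit, measurement or patient is added.
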